## Abstract

**Background:**

The use of platelet-rich plasma has been increasing in spinal fusion surgery. However, the efficacy of platelet-rich plasma in lateral lumbar interbody fusion is unclear. In Japan, Affinos,® (Kuraray Co., Tokyo, Japan), a β-tricalcium phosphate artificial bone, has been increasingly used for spinal fusion. The purpose of this trial is to demonstrate whether Affinos® impregnated with platelet-rich plasma can achieve a higher fusion rate and better clinical outcomes than Affinos® alone.

**Methods:**

The current study is a prospective randomized controlled trial. This trial will include consecutive patients scheduled for lateral lumbar interbody fusion. An intervertebral cage for lateral lumbar interbody fusion has two spaces for bone grafts. As a consequence, two bone grafts are inserted at each intervertebral level. In this study, an artificial bone with platelet-rich plasma will be inserted into one space, and an artificial bone without platelet-rich plasma will be inserted into the other space. We will compare the fusion rates between the bone grafts with and without platelet-rich plasma. Our primary endpoint will be the interbody fusion rate at 1 year after surgery.

**Discussion:**

This trial will verify the efficacy of platelet-rich plasma with Affinos® for bony fusion in lateral lumbar interbody fusion. It will also provide substantial evidence for the effectiveness and safety of platelet-rich plasma in spinal fusion surgery.

**Trial registration:**

Japan Registry of Clinical Trials (jRCT) jRCTb032200199. First registered on 13 November 2020. jRCT is approved as a member of the Primary Registry Network of WHO ICTRP.

## Background

Spinal fusion is a common surgery performed for spinal degenerative diseases, spinal fractures, and spinal deformities. The use of the lateral lumbar interbody fusion (LLIF) procedure for the treatment of lumbar spinal pathologies is increasing owing to the associated advantages of this procedure [1]. In Japan, artificial bone is used mostly as graft material for LLIF [2]. Although surgical outcomes associated with spinal fusion have improved owing to innovation in spinal instrumentation [3], bony fusion is essential to prevent pseudoarthrosis.

Affinos® (Kuraray Co., Tokyo, Japan) is a β-tricalcium phosphate artificial bone with a porosity of 57% consisting of a novel unidirectional porous structure, in which intercommunicating holes of 25–300 µm are arranged in one direction [2]. In Japan, the use of Affinos® has been increasing for spinal fusion with acceptable results, while the use of an autologous bone as a bone graft is commonly applied in many fields requiring bony fusion [2, 4].

Platelet-rich plasma (PRP) is blood plasma containing concentrated autologous platelets containing several growth factors such as platelet-derived growth factor (PDGF), transforming growth factor-β (TGF-β), and insulin-like growth factor (IGF) [5–7]. Therefore, PRP is used to accelerate bone and soft tissue healing not only in oral dentistry, dermatology, ophthalmology, and sports medicine, but also in spinal fusion surgery [8–11].

The question remains whether PRP can accelerate bony fusion in LLIF. Additionally, to the best of our knowledge, there have been no reports demonstrating the efficacy of PRP combined with β-tricalcium phosphate artificial bone in LLIF.

The purpose of this study is to demonstrate whether Affinos® impregnated with PRP can achieve a higher fusion rate and better clinical outcomes than Affinos® alone.

## Methods

### Aim

To demonstrate whether Affinos® impregnated with PRP can achieve a higher fusion rate and better clinical outcomes than Affinos® alone in the treatment of lumbar spinal pathologies using LLIF.

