**Fig. 1 Fig1:**
[figure not shown]
Schematic diagram showing the trial timeline. Consecutive patients scheduled for lateral lumbar interbody fusion will be recruited for this study. Whole blood will be drawn from each patient to prepare platelet-rich plasma. In an intervertebral cage, one space will be filled with a bone graft impregnated with platelet-rich plasma, and the other will be filled with a bone graft without PRP

GPS® III (Zimmer Biomet, Warsaw, IN, USA) will be used to prepare a PRP. A total of 52 mL of peripheral blood will be drawn from each patient before the surgery. The withdrawn blood will be centrifuged for 15 min at 3200 rpm. After elimination of platelet-poor plasma, PRP will be obtained by extracting the buffy coat layer.

CoRoent XL PEEK cage® (NuVasive, San Diego, CA, USA) will be used as an intervertebral fusion cage for the LLIF. A block-type Affinos® will be used as a bone graft in the intervertebral cage. Each cage has two spaces for a bone graft; one space will be filled with an artificial bone block impregnated with PRP, and the other will be filled with an artificial bone block without PRP (Fig. 2). Therefore, two artificial bone blocks can be grafted at each intervertebral level. The side of the bone graft with PRP will be alternately set in the order of insertion. In this way, we will assign interventions (bone graft with PRP) and controls (bone graft without PRP) randomly.

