### Data management

The personal information of patients, including medical information, will be handled in accordance with the privacy policy of the regenerative medicine provider. Each patient will be issued an ID that will permit tracing of the patient but will also protect their personal identification information using a strictly monitored ID management system.

Data managers will use the case report system to enter data. The case report system will include paper media and an electronic data capturing system. Study coordinators will verify the accuracy of data entry and check for the presence of missing data. An independent data monitoring manager, with no conflict of interest in this study will be responsible for data monitoring at the primary level.

All investigators will minimize the risks of potential adverse events. All related adverse events will be documented, and appropriate treatment will be immediately provided. An interim analysis will not be conducted.

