### Statistical analyses

For baseline characteristics, summary statistics will comprise frequencies and proportions for categorical variables, whilst means and standard deviations will be used for continuous variables. Patient characteristics will be compared using a *χ*^2^ test for categorical variables and a *t*-test or Mann–Whitney *U* test for continuous variables.

The intervertebral fusion rate in each cage space will be calculated using primary endpoint analysis. A *χ*^2^ test will be performed to compare the fusion rates between bone grafts with and without PRP.

For secondary endpoint analysis, a *χ*^2^ test will be performed to compare the fusion rates between bone grafts with and without PRP at 6 months. Multivariate analyses will be performed to assess the relationship of bony fusion with VAS, JOA-BPEQ, ODI, and EQ-5D scores.

Statistical analyses will be performed using SPSS Statistics version 27.0 (International Business Machines Corporation, NY, USA). All *p* values will be two-sided, and *p* < 0.05 will be considered significant.

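### The aim of showing better clinical outcomes with PRP cannot be tested, because every patient receives both the PRP and the non-PRP graft

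*Protocol article*

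**What the plan says.** The protocol article, under Methods, Aim, sets out to show that the PRP-impregnated graft "can achieve a higher fusion rate and better clinical outcomes than" the graft alone. The Background paragraph of the Abstract and the last sentence of the Background section state the same purpose.

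Under Study procedures, the text with Fig. 1 says that in each cage "one space will be filled with an artificial bone block impregnated with PRP, and the other will be filled with an artificial bone block without" it. The position of the PRP graft varies from cage to cage: "The side of the bone graft with PRP will be alternately set in the order of insertion". PRP is prepared for everyone: "A total of 52 mL of peripheral blood will be drawn from each patient before the surgery".

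The text after Fig. 2 lists VAS, JOA-BPEQ, ODI and EQ-5D as the fourth of four secondary endpoints. Under Statistical analyses, PRP is compared with no PRP for fusion rates only, at 1 year and at 6 months. For the scores the plan is: "Multivariate analyses will be performed to assess the relationship of bony fusion with VAS, JOA-BPEQ, ODI, and EQ-5D scores".

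The Discussion paragraph of the Abstract adds: "It will also provide substantial evidence for the effectiveness and safety of platelet-rich plasma in spinal fusion surgery".

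**The concern.** A claim that PRP improves clinical outcomes needs patients, or some other unit that carries the outcome, who differ in PRP exposure. Here the treatment contrast lies between two spaces of one cage, while the pain, disability and quality-of-life scores describe the whole patient. The article describes no PRP-free patients and no external or historical control.

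The second part of the aim is therefore stated as something to be demonstrated, yet the data will carry no information on it. The planned association between fusion and scores asks a different question: whether patients whose grafts fuse have better scores. If the aim stays as worded, that association is the only result available to answer it.

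**Working it through.** **1. The plan's own figure.** The sample size covers fusion only. Inputs from Sample size estimation: 70.9% and 94.5%, power 80%, two-sided alpha 5%. Two independent proportions, pooled variance, no continuity correction:

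- mean proportion = (0.709 + 0.945)/2 = 0.827; difference = 0.236
- n = [1.96·√(2·0.827·0.173) + 0.842·√(0.709·0.291 + 0.945·0.055)]² / 0.236²
- n = [1.048 + 0.428]² / 0.0557 ≈ 39.1, rounded up to 40 spaces per group

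The stated 40 reproduces (power at 40 is 80.9%). It is not in dispute here, and it says nothing about the clinical scores.

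**2. PRP exposure by patient.** Let patient i have Lᵢ levels, with Lᵢ from 1 to 4 (Inclusion criteria). One graft of each kind per cage gives:

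- PRP grafts = Lᵢ; non-PRP grafts = Lᵢ
- PRP share = Lᵢ/(2Lᵢ) = 0.5 for every patient
- patients with any PRP = 15; patients without = 0

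Alternating the side moves the PRP graft within the cage but does not change these counts.

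**3. Can a PRP effect on a score be estimated?** Take the model score = a + b·(PRP exposure). Exposure is constant, whether coded as any PRP (always 1) or as a share (always 0.5). The design matrix then has rank 1 instead of 2, so b is not identifiable. More patients would not change this. The number of PRP grafts does vary, but it equals both the number of levels and the number of non-PRP grafts, so it cannot separate PRP from extent of surgery.

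**4. Does the planned analysis supply the contrast?** No. It relates scores to fusion, and PRP does not enter as a compared condition.

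**5. Unit of analysis for that association.** The article does not name it. Fusion is assessed per space (40 levels × 2 = 80) and scores are per patient (15). If spaces were used as rows, each patient's score would appear 2·Lᵢ times, that is 2 to 8 times, and 80/15 = 5.3 times on average. The consequence depends on how strongly fusion clusters within patients, and the document gives no figure for that. In simulations with 15 patients, 80 rows and no true link between score and fusion, the nominal 5% test rejected as follows. The patient SD and the split of levels over patients are assumptions. Ranges span two settings, one with 70.9% fusion and one with a baseline logit of 1.5.

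| Assumed patient SD (logits) | False-positive rate, spaces as rows |
|---|---|
| 0 | about 5% |
| 0.5 | about 7% |
| 1.0 | 13–14% |
| 1.5 | 19–21% |

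With one row per patient the rate stayed at 4–5%.

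**The case against.** The strongest reply is that the trial's inferential weight rests on fusion. The primary endpoint, sample size and primary test all concern fusion, and the closing Discussion speaks of efficacy for bony fusion. The clinical scores are a secondary endpoint, and no invalid PRP-versus-control test of them is planned. This is true, and it means that the primary analysis is untouched. It does not rescue the aim, which makes the clinical claim in three places. Nor is this a detail that an unseen analysis plan could supply, because no analysis can create a comparator that the allocation lacks.

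Several stronger readings are tempting, but the document does not support them:

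- **Inflated error as a fact of the plan.** The rates above hold only if spaces are used as rows and fusion clusters within patients. The article states neither, and model details may sit in a document not shown.
- **Invalid baseline tests.** The sentence beginning "Patient characteristics will be compared using a" names no groups. Fused versus non-fused patients is a possible reading, so at most it is ambiguous.
- **Unrelated adverse events go unrecorded.** "All related adverse events will be documented" does not say that other events are left out, and it is one sentence of a condensed article.
- **Scores taken at a single time.** No measurement schedule is given. What follows from the design is one score per patient rather than per graft, at whatever times it is taken.
- **Imprecise safety data as a separate flaw.** With 15 patients, the upper 95% bound after zero events is 1 − 0.025^(1/15) = 21.8%. That is true of any 15-patient study and is not specific to this aim.

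**Conclusion.** The point holds for the aim. The clinical-outcome claim for PRP is unanswerable as designed: exposure is 15 to 0 by patient and a constant 0.5 by share, so the information on a PRP effect on VAS, JOA-BPEQ, ODI or EQ-5D is zero at any sample size. This rests only on the stated allocation, on the scores being patient-level, and on the absence of any described PRP-free or external control.

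The Abstract's promise on effectiveness and safety overreaches for the same reason: the design can inform local fusion efficacy and single-group safety, but not comparative safety. The error inflation in the association analysis is a conditional warning that rests on assumed values.

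A reader might infer that the within-cage design is itself at fault. It is not. It supports the graft-level comparison of fusion and of resorption and remodeling, and this point leaves that comparison as it stands.

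**What to change.** 1. Remove the clinical-outcome claim from the aim in the Abstract, the Background and the Aim section. Limit the PRP-versus-control claim to graft-level outcomes: fusion, and resorption and remodeling, per space.
2. Report VAS, JOA-BPEQ, ODI and EQ-5D as single-group descriptive results.
3. Label the relation of these scores to fusion as exploratory, make the patient the unit of analysis with one row each, and state that it is not evidence on PRP.
4. Narrow the Abstract's closing statement to local fusion efficacy and single-group safety.

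Keeping the clinical aim would instead need a patient-level comparator. No sample size can be given for that, because the document states no effect size or SD for any score.

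The cost is rewording and a narrower claim, with committee approval and a registry update if the change counts as an important modification under Protocol amendments. No extra patients or measurements are needed.

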### Design of the study

The study is a prospective controlled superiority trial study with randomly allocated groups.

### Study procedures

The outline of this study is shown in Fig. 1. Consecutive patients scheduled for LLIF in the University of Tsukuba hospital will be enrolled in this trial. The target sample size for this study trial is fifteen patients, with a total of 40 intervertebral levels. This trial is approved by the institutional review board of the University of Tsukuba Hospital, and consent for participation in the trial will be obtained from all patients (jRCTb032200199).

**Fig. 1 Fig1:**
[figure not shown]
Schematic diagram showing the trial timeline. Consecutive patients scheduled for lateral lumbar interbody fusion will be recruited for this study. Whole blood will be drawn from each patient to prepare platelet-rich plasma. In an intervertebral cage, one space will be filled with a bone graft impregnated with platelet-rich plasma, and the other will be filled with a bone graft without PRP

GPS® III (Zimmer Biomet, Warsaw, IN, USA) will be used to prepare a PRP. A total of 52 mL of peripheral blood will be drawn from each patient before the surgery. The withdrawn blood will be centrifuged for 15 min at 3200 rpm. After elimination of platelet-poor plasma, PRP will be obtained by extracting the buffy coat layer.

CoRoent XL PEEK cage® (NuVasive, San Diego, CA, USA) will be used as an intervertebral fusion cage for the LLIF. A block-type Affinos® will be used as a bone graft in the intervertebral cage. Each cage has two spaces for a bone graft; one space will be filled with an artificial bone block impregnated with PRP, and the other will be filled with an artificial bone block without PRP (Fig. 2). Therefore, two artificial bone blocks can be grafted at each intervertebral level. The side of the bone graft with PRP will be alternately set in the order of insertion. In this way, we will assign interventions (bone graft with PRP) and controls (bone graft without PRP) randomly.

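### The PRP side is set by alternation but called random: the allocation is quasi-random and predictable, so the label or the method has to change

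*Protocol article*

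**What the plan says.** The unit of allocation is the graft space: every cage takes two blocks, of which exactly one carries PRP (Protocol article, Study procedures, text after the Fig. 1 legend). The same paragraph gives the rule for choosing the space: "The side of the bone graft with PRP will be alternately set in the order of insertion". Its next sentence draws the conclusion: "In this way, we will assign interventions (bone graft with PRP) and controls (bone graft without PRP) randomly".

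The label appears in two other places. The abstract (Methods) says "The current study is a prospective randomized controlled trial", and Design of the study describes a "prospective controlled superiority trial study with randomly allocated groups".

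On numbers and enrolment, Study procedures states "Consecutive patients scheduled for LLIF in the University of Tsukuba hospital will be enrolled in this trial" and "The target sample size for this study trial is fifteen patients, with a total of 40 intervertebral levels". No random sequence, random starting side or concealment step is described anywhere.

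**The concern.** An article may leave the details of randomisation to the full protocol. Here, though, the mechanism is given, it is offered as the randomisation itself, and it is not random. This is a contradiction in the text and not an omission.

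Two things are at stake. First, the trial describes itself as a confirmatory randomised comparison, and readers will give it the weight that randomisation earns. Second, a predictable side can be known to anyone who knows the rule and the insertion order. That could include the operating team before the disc space is prepared and the cage seated. It could also include the three surgeons who later judge bony continuity on CT, since the article does not state whether they are blinded to side. A concealed random list would prevent both.

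**Working it through.** **Background figure.** The planned 40 spaces per group is reproduced and does not depend on the allocation method. Inputs from Sample size estimation: p1 = 0.709, p2 = 0.945, two-sided alpha 5%, power 80%. The mean rate is 0.827 and the difference 0.236.

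n = [1.960 × √(2 × 0.827 × 0.173) + 0.842 × √(0.709 × 0.291 + 0.945 × 0.055)]² / 0.236² = [1.048 + 0.428]² / 0.0557 ≈ 39.1, rounded up to 40 (power 80.9%).

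**Predictability.** There are 40 levels, hence 40 side assignments.
- Strict alternation allows 2 sequences, one per starting side. Independent random assignment allows 2^40, about 1.1 × 10^12.
- After one side is known, the next is guessed correctly with probability 1, against 0.5 under simple randomisation.
- The first side is also known in advance if the starting side is fixed. The article does not say whether it is.

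**Can a side effect leak into the PRP effect?** Suppose one side fuses better than the other by d, whatever the treatment. If a of the 40 cages have PRP on that side and b = 40 − a on the other, PRP spaces lie there in a/40 of cases and control spaces in b/40. The PRP contrast then picks up d × (a − b)/40. The result depends on whether alternation restarts in each patient, which is not stated.

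*Alternation runs on across patients.* a = b = 20, so the leak is 0. For any other total, a and b differ by at most one.

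*Alternation restarts in each patient with a fixed first side.* Splits by number of levels are 1: 1/0; 2: 1/1; 3: 2/1; 4: 2/2. So a − b equals the number of patients with an odd number of levels. With 15 patients and 40 levels:
- Smallest: ten 2-level and five 4-level patients (20 + 20 = 40). No odd patients, split 20/20, leak 0%.
- Largest: the odd count must be even because the total is even, so it is at most 14. Twelve 3-level, two 1-level and one 2-level patient give 36 + 2 + 2 = 40. The split is 27/13 and the leak is 14/40 = 35% of d.

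**Scale.** The planned difference is 94.5 − 70.9 = 23.6 percentage points. Even at the 35% extreme, a side effect would have to be 23.6/0.35 ≈ 67 points to produce that difference alone.

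**The case against.** The strongest defence is the within-cage design. Alternation usually does harm by letting investigators steer patients into arms. Here patients are consecutive and each cage receives both treatments, so patient and level factors are balanced within the cage however the side is chosen. This stands, and it rules out the classic selection bias.

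Alternation may also balance sides better than simple randomisation would. Run on over 40 cages it gives 20/20, while simple randomisation gives an expected absolute imbalance of about 5 levels (5/40 = 12.5%). This also stands, and is why the list proposed below is blocked.

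A reader might infer three stronger things that the documents do not support:
- *That the comparison is biased.* The article does not say when the side becomes known relative to disc preparation, nor that the surgeon may choose the insertion order. Bias at surgery would require treating two parts of one disc space differently. That is possible but not shown.
- *That about 20% of a side effect leaks in, from a 60/40 split.* This needs a restart in each patient, a fixed first side, and 1 to 4 levels equally likely. The last gives 15 × 2.5 = 37.5 levels (22.5 against 15), not the stated 40. Only the conditional range of 0% to 35% can be given.
- *That insertion order confounds the result.* Order is the same for both spaces in a cage, so its main effect cannot distort a within-cage contrast, and a covariate for it would not help.

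None of this makes alternation random.

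**Conclusion.** The point holds as a misstated design property. The only allocation mechanism described is deterministic, predictable at the latest from the second cage, and unconcealed as written, yet three places call it random. The correct description is alternating, or quasi-random, allocation.

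The consequence is limited. No patient or level can be moved between arms. What remains is the possibility of acting on, or reading images with, knowledge of the PRP side; the documents give no way to size it. Leakage of a side effect is zero if alternation runs on across patients. It lies between 0% and 35% of any true side effect if alternation restarts with a fixed first side, taking 15 patients and 40 levels as stated. The existence of a side effect is itself an assumption.

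**What to change.** 1. **Remaining cages, if any:** take the PRP side from a concealed, computer-generated list balanced in small blocks, revealed as late as feasible before the cage is filled.
2. **Cages already implanted, and all cages if none remain:** replace the random and randomised wording in the abstract (Methods), Design of the study and Study procedures with *alternating (quasi-random) allocation*. State how the first side was chosen and whether alternation restarted in each patient.
3. **Reporting and analysis:** report the number of PRP grafts by side. Add a sensitivity analysis of the within-cage comparison adjusted for side, for example logistic regression conditional on cage with terms for PRP and side. Do not add insertion order as a covariate.

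**Cost:** a list with a concealment step, one added analysis, and an amendment that needs committee approval and registry entry under Protocol amendments. The sample size is unchanged. The downside is that a mixed or quasi-random allocation must be reported. Recruitment began in February 2021 and the protocol version is dated April 2022, so the number of cages still open to step 1 is unknown and may be none. Steps 2 and 3 apply in any case.
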